### Statistical Analysis Plan

#### Sample Size Estimation

Our sample size was not only estimated based on our own previous work, but also based on the seminal work from Heart Failure: A Controlled Trial Investigating Outcomes of Exercise Training (HF-ACTION). At the 12-month outcome in HF-ACTION [88], 53% (n=618, 95% CI 50%-56%) of subjects in exercise training had a clinically significant improvement (≥5 points) [38] from the baseline on the KCCQ [39], compared with 33% (n=386, 95% CI 30%-35%) in Usual Care. With type I error of .05 and power of .80, 93 subjects per group are required to replicate this effect. HF-ACTION was not an e-intervention, however, it utilized a 12-month home-based program to which only 40%-45% of subjects were adherent [91]. Consequently, there was only a small treatment effect for change in exercise capacity. This was correlated with KCCQ outcomes [88]-exercise group gained only 0.6 ml^.^kg^-1.^min^-1^ (interquartile range–IQR, −0.7 to 2.3) and Controls gained 0.2 ml^.^kg^-1.^min^-1^ (IQR, −1.2 to 1.4) [92]. This is likely due to low exercise intensity. CHF-CePPORT (in keeping with our previous trials of COHRT, I-START, and REACH) [23] [19,22,28] [21] is designed to improve the quality of life associated with increased self-care behaviors, including exercise. Therefore, a similar small change in exercise capacity as in HF-ACTION is expected, in association with an expected increase in the KCCQ score [39]. With alpha of .05 and power of .80, a sample of 115 subjects per group is required. Withdrawal or drop out (for any reason) has been below 6% in HF-ACTION [93] and in our previous telemonitoring trial [24]. When completion of repeated behavioral assessments are factored into subject loss, attrition was 19% in our telemonitoring trial [24] and 21% in I-START [19,22] Therefore, we conservatively plan for 21% attrition for CHF-CePPORT-final sample=278 subjects.

Our team will recruit subjects from CHF clinics in tertiary care hospitals where we hold senior positions. It is feasible to recruit 278 subjects across 3 sites: (1) Vancouver (St. Paul’s Hospital), (2) Toronto (UHN), and (3) Montreal (Montreal Heart Institute)–Years 1 and 2=248 subjects/3 hospitals/2 years=41 subjects per hospital, per year. Additionally, 30 subjects (10 per hospital) will be recruited in the first quarter of Year 3. The research clerk at the Behavioral Cardiology Research Unit, UHN, Toronto will perform coordination and monitoring of recruitment.

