#### Statistical Analysis

This trial will use a 2 parallel-group design with 3 repeated assessments at baseline, 4-, and 12-months. A generalized mixed model (GMM) will evaluate the primary outcome, which is a binary code of whether the 12-month KCCQ [39] increases ≥5 points [38]. Predictors will include baseline KCCQ, age, sex, body mass index, and Group (e-Counseling vs Control). The primary outcome will be coded as a “failure” in the event of CHF hospitalization or mortality, but not for “elective” medical procedures (eg, cardiac resynchronization therapy). GMM with repeated measures will assess binary secondary outcomes across 4- and 12-month intervals (eg, KCCQ and smoking status). This analysis is optimal as it adjusts for serial correlations across repeated measures and between individual subjects in each group. Predictors will include baseline KCCQ, age, sex, body mass index, time (4- vs 12- month assessment interval), and Group (e-Counseling vs Control). Significant interactions or main effects will be followed by Bonferroni post hoc tests for significance, *P*<.05, 2-sided. Data missing at random will be handled by multiple imputations. For continuous secondary outcomes, linear mixed models (LMM) [94] for repeated measures with a random intercept will assess whether within-subject improvement across 4- and 12-month intervals is independently associated with our e-Counseling protocol. This analysis adjusts for serial correlations across repeated measures and between subjects in each Group. Predictors will include the baseline dependent variable, age, sex, body mass index, time (4- vs 12-month assessment interval), and Group (e-Counseling vs Control). LMM with a random intercept will also evaluate whether e-Counseling vs Control demonstrates improvement at the 12-month interval in VO_2_ peak, NT-proBNP, hsCRP, and the SHFM.

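### The 115 per group that sets the trial's size is said to give .80 power, but it follows from neither effect printed in the sample size section

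*Protocol article*

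**What the plan says.** The Sample Size Estimation section of the protocol article takes its primary effect from HF-ACTION: "53% (n=618, 95% CI 50%-56%) of subjects in exercise training had a clinically significant improvement", "compared with 33% (n=386, 95% CI 30%-35%) in Usual Care". For that contrast, at type I error .05 and power .80, it states that "93 subjects per group are required to replicate this effect".

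It then quotes the exercise-capacity results of the same trial: a gain of 0.6 ml/kg/min (IQR −0.7 to 2.3) with exercise training and 0.2 ml/kg/min (IQR −1.2 to 1.4) in controls. It goes on to say that "a similar small change in exercise capacity as in HF-ACTION is expected, in association with an expected increase in the KCCQ score". The KCCQ increase in that sentence carries no number. The next sentence reads "With alpha of .05 and power of .80, a sample of 115 subjects per group is required". Attrition of 21% is applied only after this, giving 278.

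The section also says that the size rests partly on the team's own earlier work, but prints no effect from that work.

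**The concern.** The section gives two required sizes, 93 and 115, at identical alpha and power. The first is tied to an effect. The second is not, yet it is the one that fixes the trial's size. Because the 115 comes directly after the statement about exercise capacity, a reader may take it as derived from that expectation, or take .80 as the power for it.

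Two things are at stake. The planned size and power should belong to a named difference, so that readers know what the trial was designed to detect. And peak oxygen uptake is a stated secondary hypothesis with its own planned model, so any impression that it is supported at .80 needs checking against the figures quoted.

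**Working it through.** **Inputs.** From Sample Size Estimation: 53% and 33% responders; gains of 0.6 and 0.2 ml/kg/min with their IQRs; alpha .05; power .80; 21% attrition; total 278. Assumptions: equal allocation (two parallel groups, sizes given per group) and two-sided testing. The Statistical Analysis section states two-sided testing only for its post hoc tests. (1.96 + 0.8416)² = 7.849.

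**1. The plan's 93.** n = 7.849 × [p1(1−p1) + p2(1−p2)] / (p1−p2)² per group.
- 0.53 × 0.47 + 0.33 × 0.67 = 0.2491 + 0.2211 = 0.4702
- 7.849 × 0.4702 / 0.04 = 92.3, so 93. This reproduces the stated figure.

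**2. Does the same effect give 115 under another standard method?**

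| Method, 53% v 33%, power .80 | n per group |
|---|---|
| Unpooled, two-sided | 93 |
| Arcsine, two-sided | 95 |
| Pooled, two-sided | 96 |
| Continuity-corrected, two-sided | 105 |
| Pooled, one-sided | 75 |
| Continuity-corrected, one-sided | 85 |

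None gives 115. A higher round power does not explain it either: the unpooled formula gives 106 at .85 and 124 at .90.

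**3. Power for 53% v 33% at the planned size.** Power = Φ(0.20/SE − 1.96), with SE = √(0.4702/n).
- n = 115: SE = 0.0639; Φ(3.128 − 1.96) = .88 (.87 with pooled variance).
- After 21% loss from 278: 278 × 0.79 = 219.6, or about 110 per group. SE = 0.0654; Φ(3.059 − 1.96) = .86 (.85 pooled).

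**4. Does the exercise-capacity change give 115?** This treats the reported gains as means and changes as normal, so SD = IQR width / 1.349.
- Exercise arm: 3.0/1.349 = 2.22. Control arm: 2.6/1.349 = 1.93. Pooled SD: √[(2.22² + 1.93²)/2] = 2.08.
- Standardized difference: 0.4/2.08 = 0.192.
- n = 2 × 7.849 / 0.192² ≈ 425 per group. With SD 1.93 it is 365; with SD 2.22 it is 486.
- Power at 115: Φ(0.192 × √57.5 − 1.96) = .31, with a range of .28 to .35 over the two SDs. At 110 it is .30 (.27 to .34).
- If covariate adjustment cut the SD by 10% to 20%, power at 115 would be about .37 to .45.

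For comparison, 115 per group gives .80 power for a standardized difference of √(2 × 7.849/115) = 0.37, nearly twice the 0.19 implied by the quoted figures.

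**The case against.** The best case for the plan is that nothing is miscalculated. The primary outcome is KCCQ response, its effect is stated, and 115 exceeds the 93 that this effect needs. The text expects an exercise-capacity change in association with a KCCQ increase; it never says that 115 was sized on exercise capacity, and it states no power for it. Peak oxygen uptake is a secondary measure taken from chart review. The article is condensed and refers to earlier trials, so the basis for 115 may stand in a document not shown.

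Most of this stands and limits the point. The figure of about 425 shows only that the exercise-capacity reading cannot account for 115. It does not contradict a power claim made by the sponsor.

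Condensation does not remove the point. The article prints its derivation in detail, with rates, confidence intervals and IQRs, and that derivation does not lead to 115 at .80.

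A reader might try to supply the missing origin. Three routes come close:
- 51% v 33% gives 114.1, so 115.
- 53% v 35%, using the upper limit of the quoted Usual Care interval, gives 115.5, so 116.
- 93/0.81 = 114.8, which would mean that 115 already contains the 19% attrition quoted for the telemonitoring trial, and that attrition is then counted again.

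The document states none of these. With three routes landing within a subject or so of 115, a numerical match is no evidence for any one of them. Double-counted attrition therefore cannot be asserted, and 51% v 33% cannot be presented as the planning assumption.

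**Conclusion.** The point holds as a fault in the stated basis for the sample size. At alpha .05 and power .80, 115 per group follows from neither effect printed in the section. Power at 115 is about .88 for the primary effect and about .3 for an exercise-capacity change of the size quoted.

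A reader might infer that the primary outcome is underpowered, or that a null result could not be judged against any target. Neither follows: 53% v 33% is a stated target, and power for it stays near .86 after the planned attrition.

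The primary-outcome figures assume a simple two-sided comparison of two proportions with equal groups. The exercise-capacity figures assume normal changes and SDs taken from the IQRs, but the gap from 115 to the range of 365 to 486 is too wide for those approximations to close.

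**What to change.** Keep enrolment unchanged. Replace the sentence on 115 per group in one of two ways:
- state the power that the design delivers for the stated primary effect: about .88 for 53% v 33% with 115 evaluable subjects per group, and about .86 with 110; or
- state the sponsor's own responder rates that give 115 per group at .80, if such rates were used.

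Add one sentence saying that the trial is not powered for an HF-ACTION-sized change in exercise capacity (power about .3), and that this comparison will be reported as an estimate with a confidence interval.

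The cost is one or two sentences. The downside is that the implied support for the exercise-capacity hypothesis becomes less favourable.

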**Methods:**

Canadian e-Platform to Promote Behavioral Self-Management in Chronic Heart Failure (CHF-CePPORT) is a multi-site, double blind, randomized controlled trial with a 2 parallel-group (e-Counseling + Usual Care vs e-Info Control + Usual Care) by 3 assessments (baseline, 4-, and 12-month) design. We will identify subjects with New York Heart Association Class II or III systolic heart failure from collaborating CHF clinics and then recruit them (n=278) by phone. Subjects will be randomized in blocks within each site (Toronto, Montreal, and Vancouver). The primary outcome will be improved quality of life, defined as an increased number of subjects with an improvement of ≥5 points on the summary score of the Kansas City Cardiomyopathy Questionnaire. We will also assess the following secondary outcomes: (1) diet habits, depression, anxiety, smoking history, stress level, and readiness for change using self-report questionnaires, (2) physical activity level, current smoking status, and vagal-heart rate modulation by physiological tests, and (3) exercise capacity, prognostic indicators of cardiovascular functioning, and medication adherence through medical chart review. The primary outcome will be analyzed using generalized estimation equations with repeated measures on an intention-to-treat basis. Secondary outcomes will be analyzed using repeated-measures linear mixed models with a random effects intercept. All significant main effects or interactions in the statistical models will be followed up with post hoc contrasts using a Bonferroni correction with a 2-sided statistical significance criterion of *P*<.05.

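### The 21% attrition allowance was multiplied on instead of divided out, so 278 randomised subjects leave about 110 per group rather than the required 115 (a minor planning error)

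*Protocol article*

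**What the plan says.** All of the reasoning is in the Sample Size Estimation section of the protocol article.

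- The section takes responder rates of 53% and 33% from an exercise-training trial in heart failure and says of them: "With type I error of .05 and power of .80, 93 subjects per group are required to replicate this effect".
- It then argues that a similarly small change in exercise capacity is to be expected in this trial, and concludes: "With alpha of .05 and power of .80, a sample of 115 subjects per group is required". No responder proportions, difference or standard deviation is given for this second number.
- On losses, it puts withdrawal at below 6% in two earlier trials, and then adds: "When completion of repeated behavioral assessments are factored into subject loss, attrition was 19% in our telemonitoring trial [24] and 21% in I-START".
- It ends with the total: "Therefore, we conservatively plan for 21% attrition for CHF-CePPORT-final sample=278 subjects".

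The same 278 appears in the Methods part of the Abstract ("recruit them (n=278) by phone"). It also underlies the recruitment schedule, where 248 subjects in Years 1 and 2 plus 30 in Year 3 make 278.

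**The concern.** Three planning figures stand together: 115 required per group, 21% attrition, and 278 in total. If 21% of those enrolled are lost, the number enrolled must be the required number divided by 0.79. Multiplying by 1.21 adds 21% of the smaller number and falls short. The total of 278 looks like the product of the second route.

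If so, the three figures cannot all hold. A reader who relies on the section would believe that the trial keeps 115 per group, and with it 80% power, after the full planned loss. The section also calls the allowance conservative, which would be untrue if 278 cannot absorb the loss rates that it quotes.

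**Working it through.** **Inputs, all from Sample Size Estimation:** 115 per group (230 in total), alpha .05, power .80; attrition 21%, with 19% and below 6% also quoted; final sample 278; reference effect 53% vs 33% with 93 per group. **Assumed:** 1:1 allocation (the section counts subjects per group) and a two-sided test (the article states this for its post hoc tests, not for the sample size).

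**1. Reproducing the plan's own figures.**
- 93 per group: (1.960 + 0.842)² x (0.53 x 0.47 + 0.33 x 0.67)/0.20² = 92.3, which rounds up to 93. The reference calculation is sound under the unpooled formula.
- 278 by multiplication: 230 x 1.21 = 278.3; per group, 115 x 1.21 = 139.15, and 2 x 139 = 278. This matches.
- 278 by division: 230/0.79 = 291.1. This does not match. Nor does division with the other quoted rates: 230/0.81 = 284.0 and 230/0.94 = 244.7.

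The section does not state its inflation formula. Of these routes, only multiplication by 1.21 returns 278.

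**2. What the 21% means.** It is subject loss observed in an earlier trial, so it is a share of those enrolled. The number needed is n/(1 - d): 115/0.79 = 145.6, or 146 per group and 292 in total. The gap to 278 is 14 subjects, and 14/278 is about 5%.

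**3. What 278 delivers.**
- After 21% loss: 278 x 0.79 = 219.6, or 109.8 per group, about 5 per group short of 115.
- After 19% loss: 278 x 0.81 = 225.2, or 112.6 per group, still short.
- Largest loss that leaves 115 per group: 1 - 230/278 = 17.3%.

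**4. Power at the effect for which 115 per group gives 80%.** The effect need not be known. The standardised effect at 115 per group is 1.960 + 0.842 = 2.802, and it scales with the square root of n:

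2.802 x √(109.8/115) - 1.960 ≈ 0.778, and Φ(0.778) ≈ 0.782.

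Direct calculation gives 78.1-78.2% for a difference in proportions with control rates from 20% to 45%, and for a standardised mean difference of 0.37. The result does not depend on which of these lies behind 115.

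**5. Power at the one stated effect, 53% vs 33%, with 109.8 per group.** Unpooled: 0.20/√(0.4702/109.8) - 1.960 ≈ 1.096, which gives 86.4%. The pooled formula gives 85.4%.

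**The case against.** The best case on the other side accepts the arithmetic and disputes its weight. Much of that case stands.

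- **The loss is small.** Two points of power are well within the uncertainty of a responder rate borrowed from a trial that was not an e-intervention. A reader might infer that the trial is underpowered. The document does not support that: for the only effect it states, power after the full 21% loss is still above 80%.
- **Some lost subjects still contribute.** The Statistical Analysis section plans multiple imputation for data missing at random and codes heart-failure hospitalisation or death as failure, and the Abstract specifies intention to treat. The primary outcome needs only the baseline and 12-month questionnaires. If loss for that outcome were 6%, 278 x 0.94 = 261.3 would leave about 130 per group. So 78% is best read as the power if the planned 21% is truly lost, not as a forecast. This does not repair the calculation, because the section itself treats the 21% as lost and inflates for it, and imputation does not restore all the information in an observed score.
- **The effect behind 115 is unknown.** A reader might infer that the trial was sized for about 51% vs 33%, since those rates give 80% power with 115 per group. That pair assumes a 33% control rate and a calculation on two proportions. Other control rates, or a difference in means, fit 115 equally well, and the section also cites the team's own earlier work, which is not shown.
- **The missing effect is not part of the error.** A condensed article may leave the derivation of 115 to the full protocol. Its absence is a reason to ask for it when power is restated, not a second fault.

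**Conclusion.** The planning statement is wrong as written. A requirement of 115 per group, 21% attrition and a total of 278 are incompatible: 278 comes from 230 x 1.21, and the consistent total is 292. The trial as planned keeps 115 per group only up to about 17% attrition. That is below both loss rates the section quotes once repeated assessments are counted, so the allowance is not conservative.

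The error is minor. It amounts to 14 subjects, about 5 per group, and a fall from 80% to about 78% power at whatever effect underlies 115; at 53% vs 33% power stays at about 85-86%. No outcome, analysis or decision rule is affected. These figures rest on equal allocation, a two-sided 5% test, and the section's own treatment of the 21% as subjects lost to analysis.

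**What to change.** Keep 278 and correct the sentence in one of two ways:

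- state that 278 randomised subjects preserve 115 per group for attrition up to about 17%; or
- state that 278 randomised subjects with 21% attrition leave about 110 evaluable per group, with about 78% power at the effect underlying 115 and about 85-86% for 53% vs 33%.

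In either case, drop the description of the allowance as conservative. When restating the power, the sponsor should supply the effect on which 115 rests; 51% vs 33% should not be written in as a design assumption.

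The cost is wording only, plus a slightly less favourable power or attrition figure. The Abstract and the recruitment schedule can stay as they are. If the sponsor prefers to hold 115 per group at 21% loss, the total becomes 292, with 14 more subjects to recruit and both of those places to update; two points of power do not make that necessary.

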#### Statistical Analysis

This trial will use a 2 parallel-group design with 3 repeated assessments at baseline, 4-, and 12-months. A generalized mixed model (GMM) will evaluate the primary outcome, which is a binary code of whether the 12-month KCCQ [39] increases ≥5 points [38]. Predictors will include baseline KCCQ, age, sex, body mass index, and Group (e-Counseling vs Control). The primary outcome will be coded as a “failure” in the event of CHF hospitalization or mortality, but not for “elective” medical procedures (eg, cardiac resynchronization therapy). GMM with repeated measures will assess binary secondary outcomes across 4- and 12-month intervals (eg, KCCQ and smoking status). This analysis is optimal as it adjusts for serial correlations across repeated measures and between individual subjects in each group. Predictors will include baseline KCCQ, age, sex, body mass index, time (4- vs 12- month assessment interval), and Group (e-Counseling vs Control). Significant interactions or main effects will be followed by Bonferroni post hoc tests for significance, *P*<.05, 2-sided. Data missing at random will be handled by multiple imputations. For continuous secondary outcomes, linear mixed models (LMM) [94] for repeated measures with a random intercept will assess whether within-subject improvement across 4- and 12-month intervals is independently associated with our e-Counseling protocol. This analysis adjusts for serial correlations across repeated measures and between subjects in each Group. Predictors will include the baseline dependent variable, age, sex, body mass index, time (4- vs 12-month assessment interval), and Group (e-Counseling vs Control). LMM with a random intercept will also evaluate whether e-Counseling vs Control demonstrates improvement at the 12-month interval in VO_2_ peak, NT-proBNP, hsCRP, and the SHFM.

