### Randomization and Blinding

Protection against bias will be accomplished by double blinding. Randomization will be done through a particular website which uses randomly permuted blocks to assign subjects to the e-Counseling group or to the Control group. This process will be conducted in blocks to ensure that group assignment is balanced across our recruitment sites (Toronto, Montreal, and Vancouver) for the overall trial. The individual who will be responsible for randomization at the Behavioral Cardiology Research Unit, UHN has no direct involvement in this trial. In addition, the randomization code will be hidden from trial subjects, as well as all those who will conduct assessments, data processing, and analysis. Thus, the CHF-CePPORT research team members and the trial subjects from the three sites will not be aware of the group assignment of the subjects.

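### Randomisation is blocked within three sites but none of the listed models names site; if site predicts outcome, the test of Group is conservative and some power is lost (minor)

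*Protocol article*

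**What the plan says.** The Abstract (Methods) sets the design: "Subjects will be randomized in blocks within each site (Toronto, Montreal, and Vancouver". Under Randomization and Blinding the article gives the purpose of the blocks: "This process will be conducted in blocks to ensure that group assignment is balanced across our recruitment sites". Site is the only factor named as balanced by the randomisation.

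Under Statistical Analysis there are three predictor lists:

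- Primary binary outcome at 12 months: "Predictors will include baseline KCCQ, age, sex, body mass index, and Group (e-Counseling vs Control".
- Binary secondary outcomes over both follow-up visits: "Predictors will include baseline KCCQ, age, sex, body mass index, time (4- vs 12- month assessment interval), and Group (e-Counseling vs Control".
- Continuous secondary outcomes: "Predictors will include the baseline dependent variable, age, sex, body mass index, time (4- vs 12-month assessment interval), and Group (e-Counseling vs Control".

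The 12-month linear mixed model for VO2 peak, NT-proBNP, hsCRP and the Seattle score has no list of its own and does not mention site. The dependence that the continuous models are said to handle is at the level of visits and subjects: "This analysis adjusts for serial correlations across repeated measures and between subjects in each Group". The Abstract names generalized estimating equations for the primary outcome where Statistical Analysis names a mixed model; neither description mentions site.

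**The concern.** Blocking within site forces near-equal arms in every site, so differences between sites cannot add to the chance variation of the treatment comparison. A model without site still counts those differences as residual noise. Its standard error then overstates the true sampling variability, the test rejects too rarely under the null, and power is given up.

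The article takes the trouble to name covariates model by model. It adjusts for three baseline characteristics that were not used in the randomisation and leaves out the one factor that was. At stake is a modest amount of power in a trial that plans for only 80%.

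**Working it through.** **1. The plan's own figure.** Sample Size Estimation takes responder rates from HF-ACTION: "53% (n=618, 95% CI 50%-56%) of subjects in exercise training", "compared with 33% (n=386, 95% CI 30%-35%) in Usual Care". For two proportions with unpooled variance, two-sided alpha 0.05 and power 0.80:

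n = (0.53×0.47 + 0.33×0.67) × (1.960 + 0.842)² / 0.20² = 0.4702 × 7.849 / 0.04 = 92.3, so 93 per group. This reproduces the article's 93. The article then plans on 115 per group before attrition without giving the effect size behind that number. With 33% in controls, 115 per group gives about 80% power for 51.2%, and that pair is used below.

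**2. Binary outcome, main simulation.** From the article: 115 per group, three sites, control rate 33%. Assumed: equal site sizes (77, 77, 76), permuted blocks of 4, a treatment effect constant on the log-odds scale, and site effects of −s, 0, +s in log-odds with the average rate in each arm held fixed. Around a middle site at 33%, the site rates are roughly 27/33/40% at s = 0.3, 23/33/45% at 0.5, 18/33/52% at 0.8 and 13/33/62% at 1.2. Logistic model with and without site, 20,000 runs per scenario:

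| s | Power without site | Power with site | Loss (points) | Type I error without site | Type I error with site |
|---|---|---|---|---|---|
| 0 | 81.3% | 81.3% | 0 | 5.0% | 5.1% |
| 0.3 | 81.0% | 81.1% | 0.1 | 4.9% | 5.2% |
| 0.5 | 81.1% | 81.7% | 0.6 | 4.4% | 4.9% |
| 0.8 | 82.2% | 84.2% | 2.0 | 3.9% | 4.9% |
| 1.2 | 82.9% | 87.3% | 4.4 | 3.0% | 5.0% |

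Compare across each row, not down the columns: with average rates held fixed, the within-site odds ratio grows with s.

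The mechanism shows in the standard errors under the null at s = 0.8. Without site, the model reports 0.282 on average while the estimates actually vary with a standard deviation of 0.269. With site, both are 0.297. The with-site figure is larger because the within-site odds ratio is a different quantity from the odds ratio averaged over sites. What matters for the test is that reported and actual variability agree.

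**3. Binary outcome, second set-up.** 74 evaluable per site, blocks of 4, odds ratio 2.1 (from 33%: odds 0.4925 × 2.1 = 1.034, or 51%):

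| Assumed control rates by site | Power without / with site | Loss (points) | Type I error without / with site |
|---|---|---|---|
| 28/33/38% | 76.8% / 77.1% | 0.3 | 4.9% / 5.1% |
| 23/33/45% | 74.6% / 76.0% | 1.4 | 4.5% / 5.1% |
| 15/33/55% | 66.0% / 71.3% | 5.3 | 3.7% / 5.0% |

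These are 20,000-run results, except the type I errors in the middle row (3,000 runs). The direction is the same. The middle row is somewhat larger than the main simulation gives at s = 0.5.

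**4. Continuous outcomes, closed form.** Let ρ be the share of residual variance lying between sites. With balance within site, the true standard error is √(1−ρ) times the one reported without site. If the model with site has 80% power, then without site:

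- power = Φ(2.802 − 1.960/√(1−ρ))
- type I error = 2[1 − Φ(1.960/√(1−ρ))]

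For ρ = 0.10: 1.960/0.9487 = 2.066, so power = Φ(0.736) = 76.9% and type I error = 3.9%. For ρ = 0.01, 0.05 and 0.20, power is 79.7%, 78.5% and 72.9%, and type I error is 4.9%, 4.4% and 2.8%.

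**The case against.** The best reply is that the effect depends wholly on site differences for which the article gives no figures. The primary outcome is a within-subject change of at least 5 points, and baseline KCCQ is in the model. A stable difference in level between clinics or languages largely cancels in a change and is partly absorbed by the baseline term. The simulations contain neither baseline KCCQ nor the other covariates, so they may overstate the loss. All of this stands, and it keeps the point minor. It does not remove the point, because sites may also differ in how much patients change over 12 months.

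Four stronger readings are tempting, and the article does not support them:

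- **That power is certainly lost.** It is not if sites do not differ.
- **That the benefit of blocking is thrown away.** Blocking still prevents arm-by-site imbalance and still lowers the true variability of the estimate; only the reported standard error fails to take credit for it.
- **That the predictor lists rule site out.** They say what the models will include, in a condensed article, and a random site effect in the mixed model is not excluded. Site is simply not named.
- **That the text shows site to be prognostic through language or usual care.** Materials exist in both languages without French being confined to Montreal, a validated French-Canadian KCCQ is used, and nothing says usual care differs by site.

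**Conclusion.** The point holds in conditional form and is minor. Site is the one factor the randomisation balances on, and no listed model names it. If site is prognostic, the test of Group is conservative. On the primary outcome the loss is 0 to about 0.6 power points for log-odds spreads up to 0.5 in the main simulation (1.4 points in the lower-powered set-up), about 2 points at 0.8, and 4 to 5 points only where responder rates differ by some 40 percentage points or more between hospitals. Type I error then falls to about 3 to 4%.

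A reader might infer a biased estimate or a raised false-positive risk. Neither follows: the arms are balanced within site, and the error is on the cautious side. The direction follows from the design; the size rests on assumed site rates, equal site sizes and blocks of 4.

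**What to change.** Name site (three levels, fixed effect) among the predictors of the primary model and of the generalized and linear mixed models for every outcome collected at all three sites. Put it in the matching imputation models too, so that imputation and analysis agree. Exempt the ECG heart rate variability outcome: under Secondary Outcomes only the Toronto sample provides it, so site is constant there and cannot be estimated. Make the change before unblinding, so that it is not a post hoc choice.

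The cost is two degrees of freedom and a phrase in each list. Sample size does not change, and the main simulation shows no power penalty when sites do not differ (81.3% either way).
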